### Sample size

The intervention is being implemented during training sessions and its effects measured during games. A team consists of 18 members and a game lasts ∼100 min (four quarters of ∼20 min plus ∼5 min time added on). Over a 6-month playing season, each team has ∼20 games and so each team will contribute ∼600 game-hours of exposure to knee injury risk. We used a standard cluster randomised trial sample size calculation for comparing rates between a control arm and an intervention arm.^52^ The knee injury rate in the control arm was estimated as 20 per 1000 game-hours. This figure is based on the observation of 60.2 injuries (of all kinds) per 1000 game-hours (from data from Finch *et al*^11^) and an assumption that approximately one-third of Australian Football injuries involve the knee. To have 80% power to detect a reduction in the injury rate of 35% (ie a rate ratio of 0.65) in the intervention arm compared with controls, we would require 8.8 teams in each arm. This calculation does not take account of any clustering effects of injuries by team. From the same data,^11^ we estimate that the coefficient of variation of team injury rates will be 0.35 (ie, standard deviation of team injury rates divided by mean of team rates). Assuming that the clustering effect will be identical in the intervention arm, the number of teams required must be multiplied by 2.27, ie, 8.8×2.27 = 20 teams per study arm over the 2 years. Thus 20 teams (10 in Ballarat, 10 in Perth) will be randomly allocated to each arm of the study across the two playing seasons.

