### Adjustment for, and strategies to overcome, potential confounding

A possible confounder of the relationship between the training programmes and injury outcomes are the ground conditions, particularly as the RCT is to be conducted in two different states. Research on injury in elite Australian Football players has identified ground conditions as an important factor,^54^ but this has not been explored in community-level players. Using previously published methods, a ground conditions report is obtained for all matches. This includes assessment of (*a*) soil and grass type (obtained from the groundsperson and classified as mainly couch grass, mainly rye, etc and natural sand base, sandy loam, etc) and (*b*) rainfall reading on the day of the game (obtained from a nearby weather station). If the Australian Football grounds are close to where rainfall is recorded by the Bureau of Meteorology, then it is easy to collect daily rainfall data for up to a year before.

Information on additional exercise undertaken by players is collected directly from players at both preseason and end-of-season surveys. This includes information on the type, frequency and intensity of such exercise and will be adjusted for in the analysis. Any additional exposure is expected to be evenly distributed across the two arms; therefore there is very little risk of non-differential misclassification of exposure.

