### Analysis

At the start of the RCT, retrospective injury data are obtained to determine equivalence in injury risk at baseline. Injury, exposure and compliance data are being collected during each month of the Australian Football season, and the outcome measures of interest are the total numbers of injuries, total exposure and overall compliance rates over the entire study period. All data will be pre-coded and double-entered into a PC database.

All analyses will be undertaken with the Stata analysis package and performed on an intention-to-treat basis with the control arm (arm 1) as the reference group. The analysis of biomechanical outcomes will take clustering of individuals within teams into account through the use of generalised estimating equations. Poisson or negative binomial regression, as appropriate, will be used to analyse injury rates with estimation of a scale parameter allowing for cluster effects.

Behavioural, attitudinal and knowledge variables will be assessed by a number of different items on a questionnaire. Responses will be scored, and the scores from different items combined to give an overall attitude score on a quasi-continuous scale. Scores will be compared preseason to postseason, and changes compared across study arms. The attitudes and behaviours of players, particularly attitudes before and after, will be compared by categorical data analysis again using generalised estimating equations to allow for cluster effects. Information about injury outcomes (ie, time away from sport and amount of treatment received) will be collected from all injured players so that the cost per injury can be calculated.

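### Injury rates allow for team clustering only through a scale parameter, which is valid on team totals but not on the player or match rows that the planned adjustments suggest

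*Protocol article*

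**What the plan says.** In the Analysis section of the protocol article, Poisson or negative binomial regression, whichever suits, "will be used to analyse injury rates with estimation of a scale parameter allowing for cluster effects". No team random effect, GEE or cluster-robust standard error is named for this outcome. The same section plans GEE for the biomechanical outcomes and for the attitude and behaviour comparisons. The row of data for the injury model is not stated.

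Other parts of the article point both ways.

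- Towards team totals: Analysis describes the outcomes as injuries and exposure summed over the whole study. Sample size works with team rates and the coefficient of variation between them, and concludes that "the number of teams required must be multiplied by 2.27".
- Towards smaller rows: Injury and exposure details has exposure recorded for each player. The section on adjustment for potential confounding collects additional exercise from players and says: "This includes information on the type, frequency and intensity of such exercise and will be adjusted for in the analysis". It also names ground conditions as a possible confounder and obtains a report for every match.

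**The concern.** A scale parameter, or the dispersion term of a negative binomial model, measures how much more the analysed rows vary than a Poisson count would. It carries no information about which rows share a team. When a row is a team, the excess variation of the rows is the clustering. When a row is a player or a match, the shared team effect adds little to the variance of any one row, but it adds up over all the rows of that team in the arm comparison. The scale then misses almost all of it.

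At stake is the test of the main hypothesis. The number of teams was more than doubled to pay for clustering. If the model is fitted to small rows, the standard error of the rate ratio returns to nearly the unclustered value: confidence intervals are too narrow, and an ineffective programme is declared effective more often than 5% of the time.

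**Working it through.** **Inputs**, all from Sample size unless noted.

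- Control rate: "The knee injury rate in the control arm was estimated as 20 per 1000 game-hours", so λ0 = 0.020 per game-hour; with a rate ratio of 0.65, λ1 = 0.013.
- Exposure: "each team will contribute ∼600 game-hours of exposure to knee injury risk". Check: "A team consists of 18 members and a game lasts ∼100 min", with about 20 games, gives 18 × (100/60) × 20 = 600.
- Between-team coefficient of variation k = 0.35; 20 teams per arm.
- Significance level: not stated. I assume two-sided 5%, which reproduces the article's 8.8 teams; one-sided 5% would give 6.9.

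**Step 1: the article's own figure.**

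- Without clustering: n = (1.96 + 0.842)² × (λ0 + λ1)/600 ÷ (λ0 − λ1)² = 7.85 × 0.000055 / 0.000049 = 8.81.
- Multiplier: 1 + k² × 600 × (λ0² + λ1²)/(λ0 + λ1) = 1 + 0.1225 × 600 × 0.000569/0.033 = 2.27.
- Product: 19.97, so 20 teams per arm. The stated calculation reproduces.

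**Step 2: the inflation the analysis must carry under no effect.** Both arms then have m = 0.020 × 600 = 12 injuries per team, and D = 1 + k²m = 1 + 0.1225 × 12 = 2.47.

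**Step 3: what the scale picks up.** With r equal rows per team, the expected Pearson scale is φ = 1 + k²m/r. The share of the excess recovered is (φ − 1)/(D − 1) = 1/r. Type I error is 2[1 − Φ(1.96 √(φ/D))].

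| Row | r | φ | √(φ/D) | Type I error |
|---|---|---|---|---|
| Team | 1 | 2.47 | 1.00 | 5.0% |
| Player | 18 | 1.08 | 0.66 | 19.5% |
| Match | 20 | 1.07 | 0.66 | 19.6% |

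On player or match rows the standard error is thus about 34% too small. Plain Poisson with no scale at all gives 21.2%.

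**Step 4: simulation** (20 teams per arm, 18 players per team, no effect, 8,000 trials).

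- Player rows, Poisson with Pearson scale: 19.7% with gamma team effects, 19.5% with lognormal.
- Player rows, negative binomial: about 15% (400 trials; Monte Carlo standard error √(0.15 × 0.85/400) = 1.8 points).
- Team rows: mean scale 2.44; type I error 5.2% with a t reference on 38 degrees of freedom, 6.1% with a normal reference. Negative binomial on team rows gives about 4% (400 trials).
- Player rows with robust standard errors clustered on team: 6.6% with a normal reference.

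**Step 5: sensitivity**, player rows, Poisson with Pearson scale.

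| Change (assumed) | Type I error |
|---|---|
| 22 to 40 players per team | 19.8% to 20.4% |
| 10 per 1000 h (m = 6, D = 1.74, φ = 1.04) | 12.9% |
| 5 per 1000 h (m = 3, D = 1.37, φ = 1.02) | 9.0% |
| k = 0.308 | about 17% |
| k = 0.25 | about 13% |
| Player heterogeneity, CV 0.5 or 1.0 | 17.7% or 14.6% |

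The value 0.308 is 0.35 with Poisson noise removed, on the assumption that it was computed from all-injury team rates over 600 hours: √(0.35² − 1/(0.0602 × 600)) = √(0.1225 − 0.0277).

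**The case against.** The article never says that the model is fitted to player rows. A reader might infer that it must be, because exposure, compliance and additional exercise are recorded per player. That does not follow: records can be summed to teams, covariates can be averaged, and the compliance index is not said to enter the injury model. The outcome totals and the sizing on team rates fit a team-level analysis at least as well, and there the stated method holds its level. The use of GEE for some outcomes and a scale for injury rates need not be an oversight either: it also fits individual measurements on one side and aggregated rates on the other. Finally, the unit of analysis is a detail that a condensed article may leave to a fuller document.

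Most of this stands. It rules out presenting 19% as the error rate of the plan. It does not dispose of the point, because the article does more than omit a detail. It fixes one clustering device, and it also plans adjustment for a variable measured on players and treats one measured on matches as a possible confounder. Used as recorded, these call for rows on which that device fails. The article does not say that they will be summarised to team level.

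**Conclusion.** The sentence is valid for one unstated choice of row and seriously anti-conservative for the others. On team totals the type I error is about 5 to 6%. On player or match rows it would be about 19 to 20% for Poisson with a Pearson scale at the article's own inputs. Over the event rates, coefficients of variation and player heterogeneity tried on player rows, the range is about 9 to 20%. These figures assume a two-sided 5% test; the base figure also assumes that k = 0.35 carries over from all injuries to knee injuries.

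A reader might conclude that the trial's main test has a type I error of 19%. The document does not support that, since it permits the team-total reading. I would rank this as a cheap improvement rather than a correction without which the analysis fails.

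**What to change.** Replace the sentence in Analysis with one of the following.

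- Injury rates are analysed by Poisson or negative binomial regression with a log-exposure offset, and with either a team-level random effect or GEE or robust standard errors clustered on team, using a t reference or another small-sample correction. This suits any row unit and matches the GEE already planned for the biomechanical and attitude outcomes. The correction is worth naming because the uncorrected robust version gave 6.6%.
- Or: the model is fitted to one row per team, the scale is estimated on team degrees of freedom with a t reference, and player and match covariates are summarised to team level.

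The cost is one sentence; no new data are needed. Compared with a scale estimated on player rows, intervals on the log scale would be about √(2.47/1.08) = 1.5 times as wide at the article's inputs. That is the width the sample size already provides for.

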For continuous biomechanical outcome data measurements, we plan to sub-sample six players per team. Given 20 teams per study arm, this will give us 80% power to detect effects of size (*a*) 0.44 or (*b*) 0.63 standard deviations (SDs) between study arms assuming a clustering effect described by an intracluster correlation coefficient of (*a*) 0.1 or (*b*) 0.4. The SDs refer to total player-to-player variability in the biomechanical outcome, and the intracluster correlation coefficient is the ratio of between-team variability to total variability. To achieve six players with complete biomechanics data, we will enlist eight, expecting ∼20% dropout based on our previous training study. These sample size calculations also provide a conservative lower bound for power for the analysis of attitude scores, as they were based on six players per team, and the change in attitude scores will be available for closer to 18 players. The study will therefore have >80% power for detecting changes in neuromuscular, biomechanical and attitude parameters as described by an effect size of 0.44 SDs.

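### The attitude score is built and powered as a near-continuous measure, but the only method named for attitudes is categorical: a mismatch with a modest, avoidable loss of precision

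*Protocol article*

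**What the plan says.** The Analysis section of the protocol article describes how the behavioural, attitudinal and knowledge items are scored, with "the scores from different items combined to give an overall attitude score on a quasi-continuous scale". It then says that scores are compared from preseason to postseason and that changes are compared between arms, without naming a model for that comparison. The next sentence does name a method: "The attitudes and behaviours of players, particularly attitudes before and after, will be compared by categorical data analysis again using generalised estimating equations". The GEE is there to handle clustering.

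The Sample size section treats the same outcome as continuous. It starts from the biomechanical measures, for which "we plan to sub-sample six players per team". It reports: "Given 20 teams per study arm, this will give us 80% power to detect effects of size" of "0.44 or (*b*) 0.63 standard deviations (SDs) between study arms", for ICCs of 0.1 and 0.4 respectively. It then carries the result over to attitudes: "These sample size calculations also provide a conservative lower bound for power for the analysis of attitude scores". The reason given is that the calculation used six players, whereas "the change in attitude scores will be available for closer to 18 players". The section closes by claiming more than 80% power for attitude parameters at 0.44 SD.

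**The concern.** The two sections do not describe the same analysis. A power figure in SD units belongs to a comparison of means. A categorical analysis of an overall score requires the score to be grouped first, and the article gives no reason for grouping, no number of groups and no cut-points.

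Three things follow if the score is grouped:

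- Information already collected is discarded, so a real shift in attitudes is more likely to be reported as no change.
- The choice of cut-points becomes an extra analytic decision that a comparison of means does not need.
- The power statement stops applying to the test that is run.

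Changes in player attitudes matter to the trial's own purpose. The Outcomes and Significance section lists them among the possible unintended effects that need to be monitored. The injury-rate analysis is not affected.

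**Working it through.** **Inputs from the Sample size section:** 20 teams per arm; m = 6 players per team (biomechanical sub-sample, used as a lower bound for attitudes) or about 18 (expected for attitudes); effect d = 0.44 SD with ICC 0.1, or 0.63 SD with ICC 0.4.

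**Assumptions:** two-sided 5% test (not stated in the article, but it reproduces its figures); normally distributed score; exactly 18 players per team where the article says close to 18.

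**Step 1. Reproduce the article's power.** Effective players per arm: n = 20m / [1 + (m − 1) × ICC]. Power = Φ(d / √(2/n) − 1.96).

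- m = 6, ICC 0.1: n = 120/1.5 = 80; standard error √(2/80) = 0.158; 0.44/0.158 = 2.78; power 79.5%.
- m = 6, ICC 0.4: n = 120/3 = 40; standard error √(2/40) = 0.224; 0.63/0.224 = 2.82; power 80.4%.

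Both agree with the stated 80%, so the article's figure is a comparison of means.

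**Step 2. Full scale at the attitude sample size.** m = 18, ICC 0.1: n = 360/2.7 = 133.3; standard error 0.1225; 0.44/0.1225 = 3.59; power 94.9%.

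**Step 3. Two-way split midway between the arm means, m = 18.** The shares above the cut are Φ(0.22) = 58.7% and 41.3%, a difference of 17.4 points.

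- ICC kept at 0.1: n = 133.3. Standard error 0.0612 under no difference and 0.0603 under the alternative. Power = Φ[(0.1741 − 1.96 × 0.0612)/0.0603] = 82%.
- ICC converted to the binary scale, (2/π) × arcsin(0.1) = 0.064: n = 360/(1 + 17 × 0.064) = about 173; power 90%. Converting the ICC at the exact cut and using the unpooled standard error gives 91%.

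**Step 4. Uneven split, m = 18.** With 20% of controls above the cut, the other arm has 34.4% above it. Power is 76% with the ICC kept at 0.1, 86% with the converted value of 0.064, and 88% with the ICC converted exactly for each arm's share.

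**Step 5. Number of categories.** Simulated power, comparing team-level summaries (6,000 runs, 0.44 SD, ICC 0.1):

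| Players per team | Full scale | Two categories | Three | Five |
|---|---|---|---|---|
| 6 | 80% | 67% | 73% | 77% |
| 18 | 94% | 90% | 92% | 93% |

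**Step 6. The six-player lower bound.** A midpoint split at m = 6 gives 60% (ICC kept), 65% (ICC 0.064) or 67% (exact conversion, unpooled standard error). A cut at the control median with exact conversion gives 66%.

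**The case against.** The strongest reply is that the Analysis section makes two statements, not one. The first says that changes in score are compared between arms, and this is the comparison the Sample size section powers. The second, on categorical GEE, speaks of attitudes and behaviours and does not mention the score, so it may refer to individual questionnaire items, for which categorical methods are natural. On that reading only the model for the score is left unnamed, which a condensed article may fairly leave to the analysis plan.

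This reading is possible, but the text does not state it. The categorical sentence singles out attitudes before and after, which is the comparison the score was built for, and no other method is named for attitudes. The point is a mismatch between what is named and what is powered, not a missing detail. If the item-level reading is intended, the same one-sentence edit makes it explicit.

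The reply is right on size. A reader might infer that power falls to about 66% instead of the stated 80%. The article does not support that. Six players per team is declared a lower bound for attitudes: "conservative lower bound for power for the analysis of attitude scores, as they were based on six players per team". The 66% needs both that bound and a two-way split, and the article mentions no such split.

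**Conclusion.** The point holds as a mismatch of scale and method. The attitude score is near-continuous and powered as such, while the only method named for attitudes is categorical.

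If the score is split in two, the chance of missing a 0.44 SD shift at 18 players per team rises from about 5% to about 9–18% with a split near the middle, and to about 12–24% with the uneven cut. With three to five ordered categories the simulated loss is 1 to 2 points. These figures assume a normal score, an ICC of 0.1, 18 players per team and a grouping that the article does not specify. The claim of more than 80% power survives an ordinary split; in these calculations it fails at 18 players only for the uneven cut with the ICC left unconverted.

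The severity is minor: attitudes are a secondary behavioural component, and the change is a free improvement.

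**What to change.** In the Analysis section, state that the change in overall attitude score is compared between arms on its quasi-continuous scale, using a GEE for a continuous outcome with team as the cluster. Report it as a mean difference with a 95% confidence interval and robust standard errors. Reserve categorical GEE for individual items that are categorical by nature.

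The wording should specify the continuous-outcome model outright. It cannot simply point to the biomechanical analysis, because the article names only generalised estimating equations there, with no distribution or link.

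The cost is one sentence. The data, the Stata package and the GEE approach stay as planned, and the SD-based power statement then describes the analysis that is run. A mean score difference is slightly less intuitive than a percentage, but a descriptive table of grouped scores can still be shown.

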### Project time frame

The project is being conducted over the 4-year period of 2006–2009 (including two playing seasons) as shown below. Given the timing of the Australian Football season, and the need to produce the training instruction kits, data collection forms, and to set-up the biomechanical testing procedures, the trial phase itself did not start until year 2.

Jan–Mar 2006: Staff advertising and appointmentMar–Dec 2006: Preparation of data collection forms/setting-up of biomechanical field testing procedures/production of training instruction kits/pilot testing of attitudinal survey proceduresJan–Mar 2007 (and Jan–Mar 2008): Recruitment of teams and players/randomisation/training of PDCsMar–Apr 2007 (and Mar–Apr 2008): Attitudinal surveysMar–Aug 2007 (and Mar–Aug 2008): Implementation of interventions/injury surveillance/exposure monitoring/compliance checks/biomechanical studiesSep–Dec 2007 (and Sep–Dec 2008): Data entry/database management/preliminary data analysis2009: Data analysis and publication writing

## OUTCOMES AND SIGNIFICANCE

Sports injury prevention efforts to date in Australia have been severely hampered by the lack of evidence supporting currently advocated countermeasures. This concern has been recognised by the NHMRC. It is now time to implement and formally evaluate the effectiveness of sports injury countermeasures in the context of broad community level participation in sport, in contrast with previous research focused on professional sport, and deliver the preventive measures to the community. Focusing attention on demonstrating the effectiveness of Australian Football injury interventions in the field will establish Australian leadership in sports safety research and assist the delivery of safe sport in Australia. Sports participants will benefit through safer sporting environments that ensure that maximum participation and its associated health benefits can be achieved over a full lifespan.

In order to progress sports safety efforts in this country, it is important to demonstrate that the implementation of any sports safety strategy, such as exercise training regimens, achieves its desired objectives (ie, increased adoption rates and reduced injury rates). In addition, any unexpected adverse effects of safety measures, eg, any changes in participation rates and player attitudes and/or behaviours need to be monitored. To date, there have been very few internationally published formal evaluations of any sports injury prevention measure such as training programmes. From a public health perspective, it is necessary to act at the broad community level of play because of the large numbers of participants at these levels. National, state and local sports bodies can only begin to develop and implement “best practice” injury prevention when they can identify injury priorities and effective strategies for their prevention, based on a firm evidence base. Rigorous research and evaluation of effective countermeasures is therefore required to progress sports safety in Australia. A major strength of this project is the application of fully piloted basic laboratory work to the real-world setting to address a problem of public health significance through the uniting of epidemiological and biomechanical approaches.

Most knee injuries (over 60%) in community-level Australian Football are not associated with body contact. Our interventions have the potential to reduce the incidence of both contact and non-contact injuries, because they will improve the knee’s resistance to forces placed on the lower limb joints during such contact. All injuries, irrespective of their body site or cause, will be recorded in players from each RCT arm so that this can be ascertained.

For logistical reasons, this study is being conducted on Australian Football players only. However, it has significant potential to inform injury prevention efforts in other sports with a significant risk of knee injury (eg, women’s netball). It will do this in four ways.

Few large-scale RCTs of knee injury prevention exercise programmes in any sport have been previously reported in the international literature; this project will therefore inform the design and conduct of future studies.It will provide valuable guidance on how to work with sporting bodies, coaches and players to maximise the uptake of injury interventions.The training programme is a general one which could, should it prove effective, be immediately applied to other sports.It will provide further confidence in linking the results of laboratory-based biomechanics injury research to large-scale community-based RCTs, thus supporting this research model to produce solutions to injury problems.
